## Abstract

Infections, particularly those involving the respiratory tract, are associated with an increased incidence of cardiovascular events, both de novo and as exacerbations of pre-existing cardiovascular diseases. Influenza vaccination has consistently been shown to reduce the incidence of cardiovascular events. Nonetheless, vaccination rates among adults remain suboptimal, both in the general population and among high-risk individuals. Multiple barriers hinder achieving adequate vaccination rates, with physicians’ beliefs and attitudes towards these interventions being crucial.

The FLUence project was developed within the framework of the World Heart Federation’s Emerging Leaders program, to address this issue. This project has two phases: a global quantitative survey to assess the perceptions, opinions, and attitudes and challenges of physicians worldwide regarding the safety and efficacy of the influenza vaccination use, and a qualitative survey to further investigate the barriers and facilitators of recommending and using this vaccination. The quantitative survey was created and disseminated in five languages (English, Spanish, French, Italian, and Portuguese) to physicians of all specialties who care for adults, with a particular focus on patients with cardiovascular disease. The survey included eight domains with a total of 36 questions with closed options; a Likert scale with five possible answers was used to gauge participants’ opinions.

To gain deeper insights into the complexities behind the low vaccination rates in adults, the second part of the project comprises a qualitative survey, conducted in the two lower-middle- and upper-middle-income countries: India and Argentina, respectively. These countries were selected because patients with cardiovascular diseases have access to free influenza vaccination in Argentina, whereas patients must pay for the vaccine out of pocket in India.

Thus, the FLUence study will provide valuable information to better understand the perceptions and barriers to improving influenza vaccination rates from the perspective of physicians. It is imperative to actively engage all healthcare providers to improve influenza vaccination rates.

## Background

For centuries, infectious diseases were the leading cause of death worldwide. From the early twentieth century, changes in the environment, by means of urbanization, improved sanitation and the advent of simple preventive and therapeutic measures such as vaccination and antibiotics, led to a reduction in the burden of infectious diseases (1,2,3). Cardiovascular diseases (CVD) have subsequently become the leading cause of death worldwide with an estimated 17.9 million people dying from CVD in 2019 (4). It is worth noting that in Low- and Middle-Income Countries (LMICs), while infectious diseases continue to show a significant burden, CVD and other non-communicable diseases have now taken over (5).

Over the past few decades, there is increasing evidence to suggest links between acute infections (both viral and bacterial) and cardiovascular events (6,7,8,9). In several observational studies, acute thrombotic events such as acute coronary syndrome (ACS) and stroke were seen to be associated with the occurrence of a preceding acute infection, in particular infections of the respiratory tract (1,6,7,8,9,10,11,12,13,14). Up to one-third of ACS events are preceded by respiratory symptoms (6,15,16). This risk is highest during the first days after infection and gradually decreases over time (10,13,15,17,18). In addition, respiratory infections have been associated with a worsening of pre-existing cardiovascular conditions (1,19,20,21,22).

A systematic review of observational studies demonstrated that influenza is a trigger for acute myocardial infarction with a seasonal effect observed such that increased mortality due to cardiovascular disease were reported during times when influenza was circulating (11). In this context, several systematic reviews and meta-analyses have shown that influenza vaccines reduce cardiovascular morbimortality (23,24,25,26). Furthermore, the IAMI trial randomized patients after an acute myocardial infarction or high-risk percutaneous angioplasty and found that those who received the influenza vaccine during the hospitalization exhibited fewer major adverse cardiovascular events at 12 months of follow-up (27).

This comprehensive evidence has led scientific societies to develop consensus guidelines regarding influenza vaccination for high-risk patients with CVD (28,29,30,31). However, available data suggest that in most countries, vaccination rates fall far below the World Heart Organization’s 75% target for high-risk patients (32,33,34,35). For instance, data from the general population in Argentina indicate a vaccination rate of 37.7% (32), while the rate among patients with cardiovascular disease is about 65% (33). In India, studies have shown that influenza vaccination rates among physicians range from 4.4% to 54.8% (36). In a community survey conducted in Pune, India, only 8.3% of participants reported having received the influenza vaccine, and 10.6% stated that a household member had received it (37).

Several factors, including patient, provider, and access issues are implicated in the low uptake of influenza vaccination in various settings (38). There is a paucity of data regarding what factors on the provider-side contribute to the low uptake in patients with CVD. Hence, in the FLUence project, we aim to explore the physician’s knowledge, attitude, and practice regarding influenza vaccination among patients with cardiovascular diseases and to investigate the variability of these factors across different settings.

## Methods and design

### Study design

The FLUence project will employ a mixed-methods approach, incorporating both a quantitative survey and a qualitative component, which will include in-depth interviews conducted in India and Argentina.

#### Quantitative survey

A cross-sectional electronic survey was designed and implemented following the Consensus-Based Checklist for Reporting of Survey Studies (CROSS) proposed by the Enhancing the Quality and Transparency of Health Research (EQUATOR) Network and the CHERRIES checklist (39,40). The survey was conducted from October 2023 to June 2024. Using *SurveyMonkey^®^* we prevented duplicate responses from the same IP addresses.

The survey included eight domains with a total of 36 questions with closed options. The selected domains were:

General informationKnowledgePerceived riskPerceived benefitsSelf-efficacyKnowledge gaps and training needsBarriers to immunizationFinal questions related to practical implementation

These questions aimed to capture demographics, profession, work environment, level of work experience, and the knowledge, attitude, and practice of participants regarding prescribing or encouraging influenza vaccination among patients with CVD. It also captured the current practice processes in the participants’ jurisdictions in terms of vaccine prescribers/providers and inclusion of those recommendations in regional and local professional guidelines (Supplementary material I).

A Likert scale with five possible answers was used to gauge participants’ opinions on different aspects of vaccination. The only exception was the question related to respondents’ opinion regarding the benefit of influenza vaccine to patients with high cardiovascular risk, for which we provided four options: ‘No benefit,’ ‘Little benefit,’ ‘Great benefit,’ and ‘Not sure.’

The questionnaire link was distributed via email through the World Heart Federation mailing list and other associated scientific societies, in five languages: English, Spanish, French, Italian, and Portuguese.

##### Study population

Physicians from any country who provide care to adult patients were invited to participate in the quantitative survey. We aim to reach over 3,500 physicians worldwide.

Participation in the survey is voluntary, and all respondents have the option to decline participation. To protect and ensure the confidentiality of participants’ personal information, informed consent was implied by voluntary completion of the survey (*see Ethical consideration*).

#### Qualitative survey

The qualitative phase of the study will be conducted between August 2024 and March 2025. We will utilize a qualitative method of inquiry through in-depth, semi-structured interviews with stakeholders involved in the delivery of CVD prevention and management. These interviews will gather rich data grounded in personal experiences, considering the interviewees as experts in their own experiences. This approach will help identify the barriers and facilitators to the uptake of influenza vaccination in patients with cardiovascular diseases in the two lower-middle- and upper-middle-income countries: India and Argentina, respectively. Notably, the influenza vaccine is freely available for people with cardiovascular diseases in Argentina.

The qualitative interviews will collect data on providers’ thoughts, feelings, motivations, and the social processes and practical issues that drive or hinder vaccination. This information will help develop evidence-informed strategies to increase uptake among high-risk patients and the general public.

We have employed the Behavioural and Social Drivers (BeSD) framework (Figure 1) for the qualitative phase of the study (41). This framework enables vaccination uptake programs to design, target, and evaluate interventions for greater impact and efficiency and to examine and understand trends over time. Briefly, the behavioral and social drivers of vaccination are defined as beliefs and experiences specific to vaccination that are potentially modifiable to increase vaccine uptake (41). Typically, four domains will be measured by this framework (Figure 1):

thoughts and feelings about vaccines.social processes that drive or inhibit vaccination.motivation or hesitancy to seek vaccination.practical issues involved in seeking and receiving vaccination.

**Figure 1 F1:**
[figure not shown]
The Behavioural and Social Drivers (BeSD) framework. Adapted with modifications from reference (41): ‘Behavioural and social drivers of vaccination: Tools and practical guidance for achieving high uptake’, World Health Organization 2022.

Specific to this qualitative section of our proposal, the BeSD framework allows the capture of broader factors influencing stakeholders’ responses, such as political perspectives, socio-economic status, literacy, or other factors not covered in the quantitative survey.

##### Study setting and recruitment

We will recruit provider-level stakeholders identified by the researchers. Recruitment of stakeholders will be conducted in both public and private healthcare settings in India and Argentina. In each of these countries, we will include physicians treating patients with CVD (n = 8), nurses, educators, dietitians (n = 5), pharmacists (n = 4), and policymakers (n = 5). The two partner institutions for recruitment and conducting the qualitative interviews are the Madras Diabetes Research Foundation (MDRF) in India and NEUmonologia y Corazon Organization for Research (NEUCOR) in Argentina (see Figure 2, *Flow Chart Diagram*). Recruitment for healthcare providers and policymakers will occur through the extensive local networks of the research team.

**Figure 2 F2:**
[figure not shown]
Recruitment of the participants for the qualitative phase of the project.

##### Interview guide development and interview process

The interview will be based on the Behavioral and Social Drivers (BeSD) framework, supplemented by insights from other relevant previous studies (41,42). This approach ensures that the guide is comprehensive and tailored specifically to the health provider stakeholder group, as detailed in Table 1. Interviews will be conducted by a trained qualitative researcher who is fluent in the participants’ language, ensuring clear and effective communication. Each interview will be scheduled to last approximately one hour, providing ample time to explore the topics in depth. The interviews will be conducted in a private setting to ensure confidentiality and encourage open and honest responses from participants.

**Table 1 T1:** Conceptual framework for the qualitative study.

BARRIERS AND FACILITATORS IN THE UPTAKE OF INFLUENZA VACCINATION IN PATIENTS WITH CARDIOVASCULAR DISEASES IN INDIA AND ARGENTINA	

CATEGORY	FACILITATORS AND BARRIERS

Health Care provider/Physicians	Awareness, need, misinformation, motivation, self-belief, patient hesitation

Health care provider/other groups	Awareness, self-belief, other sources, negative perception, patient hesitation

Policy makers	Insurance coverage, bureaucracy hurdles

Each interview will be audio-recorded with the participants’ consent, allowing for detailed and accurate data collection. The recordings will facilitate thorough review and analysis, ensuring that nuanced insights and key points are captured. To enhance the reliability of the data, the interviewer will immediately transcribe their initial reflections and observations following each interview. These transcriptions will include notes on non-verbal cues, the interview context, and any emergent themes or unexpected topics discussed during the session.

##### Ethical consideration

The project has been approved by the Executive Board of the World Heart Federation and is currently under review by the Ethics Committee of the Madras Diabetes Research Foundation in India and the Ethics Committee of the Faculty of Medicine at the National University of Rosario (UNR) in Argentina. To ensure the honesty of responses without fear of judgment, and given that all respondents were healthcare providers, participants were not asked to complete a written informed consent form. Instead, consent was implied by the voluntary completion of the survey.

##### Data analysis of the quantitative survey

A non-probability snowball sampling will be performed. Demographics and participant characteristics will be presented using descriptive statistics. Continuous variables will be expressed as mean and standard deviation or median and interquartile range, according to their distribution. The normality of each variable will be evaluated using graphic tools (histograms and normal probability plots) and the Shapiro-Wilk test. The categorical variables will be presented as numbers and percentages.

We will categorize the participants based on the scores in terms of knowledge, attitude, and practice and will compare the levels across the participating sites using the Chi-square test or Fisher’s exact test depending on the frequency of expected values. The student’s T-test will be used for comparisons of the normally distributed continuous variables between groups.

Multiple logistic regression models will be constructed to explore the variables associated with positive attitudes and practices toward influenza vaccination. All variables that achieve a p-value of ≤0.2 in the univariate model will be included in the multivariable regression model, along with those deemed clinically relevant by the investigators. All tests will be two-tailed, and a p-value <0.05 will be considered statistically significant. The analyses will be performed using STATA (Version 18.0, Stata Corp., College Station, TX, USA).

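### The stated logistic models treat physicians from many countries as independent, so standard errors and p-values for country-patterned predictors may be substantially too small

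*Protocol article*

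**What the plan says.** *Data analysis of the quantitative survey* sets out the methods. For the models: "Multiple logistic regression models will be constructed to explore the variables associated with positive attitudes and practices toward influenza vaccination". Variables enter the multivariable model if their univariate p-value is at most 0.2 or if the investigators consider them clinically relevant. For group comparisons the plan "will compare the levels across the participating sites using the Chi-square test or Fisher’s exact test depending on the frequency of expected values", and "The student’s T-test will be used for comparisons of the normally distributed continuous variables between groups". The threshold is fixed: "All tests will be two-tailed, and a p-value <0.05 will be considered statistically significant".

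The same section gives the sampling method: "A non-probability snowball sampling will be performed". *Study population* defines who could answer: "Physicians from any country who provide care to adult patients were invited to participate in the quantitative survey". *Quantitative survey* gives the channel: "The questionnaire link was distributed via email through the World Heart Federation mailing list and other associated scientific societies". The recruitment aim is stated as "We aim to reach over 3,500 physicians worldwide", without a derivation.

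The article mentions no random effect, generalised estimating equation, cluster-robust standard error or mandatory country term. *Anticipated Limitations* acknowledges heterogeneity between contexts, but only as a difficulty for uniform policy.

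**The concern.** Physicians in one country share its vaccine supply, its guidelines and its rules on who prescribes and who gives the vaccine. Many will also share a society or a referral chain. Their answers are therefore likely to be correlated. Logistic regression in its standard form assumes independent respondents.

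The consequence depends on the predictor. *Quantitative survey* says that the questionnaire collects the local process for prescribing and providing the vaccine, and whether regional and local guidelines include it. Both are likely to vary largely by country. For such predictors the information lies mostly in the differences between countries, and the number of respondents overstates it. Intervals would be too narrow, and chance differences between countries could be reported as determinants of attitude or practice. *Background* makes variability across settings an aim, and *Discussion* expects the results to inform recommendations to policy makers.

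**Working it through.** **Inputs from the article.** N = 3,500 (the recruitment aim); two-sided alpha 0.05; univariate screen at 0.2. There is no power figure, ICC or number of countries to reproduce.

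**Assumptions.** Number of countries K from 20 to 100; country ICC from 0.01 to 0.10; country sizes equal or with coefficient of variation (CV) 1.5.

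**Step 1: formula for a fully country-level predictor, equal sizes.** With m = N/K:
- design effect DE = 1 + (m − 1) × ICC
- the standard error is understated by a factor √DE
- effective N = N/DE
- actual alpha = 2 × [1 − Φ(1.96/√DE)]

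For K = 40 and ICC 0.05:
- m = 3,500/40 = 87.5
- DE = 1 + 86.5 × 0.05 = 5.325
- √5.325 = 2.31
- effective N = 3,500/5.325 = 657
- actual alpha = 2 × [1 − Φ(1.96/2.31)] = 2 × [1 − Φ(0.85)] ≈ 0.40

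**Step 2: range.** Values are for ICC 0.01 / 0.05 / 0.10.

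| Countries | DE | Actual alpha |
|---|---|---|
| 20 | 2.74 / 9.70 / 18.40 | 0.24 / 0.53 / 0.65 |
| 50 | 1.69 / 4.45 / 7.90 | 0.13 / 0.35 / 0.49 |
| 100 | 1.34 / 2.70 / 4.40 | 0.09 / 0.23 / 0.35 |

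**Step 3: does it depend on the predictor?** The formula covers only the extreme case. A simulation (N = 3,500, no true effect, random country intercept, ordinary univariate logistic Wald test at 0.05, 1,000 runs per cell) varied how much of the predictor lies between countries. Actual type I error for ICC 0.01 / 0.05 / 0.10:

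| Predictor | 50 equal countries | 20 countries, CV 1.5 |
|---|---|---|
| Fully country-level | 0.12 / 0.31 / 0.43 | 0.35 / 0.61 / 0.73 |
| 20% of latent variance between countries | 0.06 / 0.08 / 0.13 | 0.10 / 0.25 / 0.33 |
| No between-country variation | 0.05 / 0.06 / 0.07 | 0.07 / 0.05 / 0.04 |

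The simulation defines the ICC on the underlying logistic scale, which corresponds to a somewhat smaller correlation on the yes/no scale. Its figures for the fully country-level predictor are therefore a little below those of the formula. The last row is nominal within simulation error: the Monte Carlo standard error at 0.05 is √(0.05 × 0.95/1,000) ≈ 0.007.

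**Step 4: the screen.** At K = 40 and ICC 0.05, a null country-level variable passes the 0.2 screen with probability 2 × [1 − Φ(1.28/2.31)] ≈ 0.58, against the intended 0.20.

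**The case against.** Four arguments on the other side carry weight.

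- **Independence is inferred from silence.** This is a condensed article, and a fuller analysis plan may state the variance estimator. Country may also enter the model through the screen or as clinically relevant. That stands as a caution. However, the article names its methods without qualification and does not require a country term. If country entered as fixed indicators, it would absorb between-country differences for physician-level predictors, but a purely country-level predictor could then no longer be estimated.
- **Most predictors may be physician-level.** The questionnaire mainly covers demographics, profession, work environment, experience, knowledge, attitude and practice. A reader might infer that all standard errors and p-values will be far too optimistic. The documents do not support that: the simulation shows near-nominal error for predictors without between-country variation. A reader might also take free versus paid vaccine or country income level to be planned predictors. The article names no predictors, and it raises those two features only in choosing, or limiting the reach of, the two-country qualitative phase. Guideline inclusion and prescribing process are surveyed, but each physician reports them, so they are country-patterned rather than fixed by country.
- **The chi-square test compares sites directly.** A reader might conclude that this test is invalid too. It is not invalidated by clustering on site, because the difference between sites is the effect sought. Only dependence within a site, through societies or referral chains, remains. The error rates above do not describe that test.
- **The models are exploratory.** This lowers the severity. It does not remove the point, because a 0.05 threshold is set and the results are meant to inform recommendations.

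**Conclusion.** The concern holds in a limited form. Run as written, the logistic models ignore dependence between physicians of the same country, and for country-level or strongly country-patterned predictors the p-values may be substantially too small. The error is large for a fully country-level predictor (about 0.40 with 40 equal countries and ICC 0.05), modest to large for a partly patterned one, and about nil for a purely within-country one. It is worst with few countries of very unequal size. All of these sizes rest on an assumed ICC and an assumed number and size distribution of countries, because the article gives none of them. For an exploratory analysis this should be fixed, but it does not invalidate the study.

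**What to change.** - Fit both the univariate screening models and the multivariable logistic models with a random intercept for country. Country-clustered robust standard errors are an alternative if countries are numerous. A random intercept keeps country-level predictors estimable.
- Use the same approach for group comparisons, including those now planned with a t-test, where the groups are made up of several countries or are themselves country-patterned.
- Keep the chi-square or Fisher test where site or country is itself the factor compared. A country random intercept would absorb that comparison.
- Report the country ICC and the number of respondents per country.

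**Cost.** A change of wording and of model command. No new respondents are needed, provided that country was recorded, which the planned comparison across sites suggests. The downside is wider intervals and fewer significant country-patterned associations.

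**What it leaves open.** A country intercept does not deal with dependence by society or referral chain, nor with the selection bias of a non-probability sample. Both should be stated as limitations.

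### The survey regression screens physician factors on crude p-values across pooled countries and does not fix country in any model, so real within-country factors can be lost and null ones can look significant

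*Protocol article*

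**What the plan says.** The model-building rule is in the protocol article under Data analysis of the quantitative survey: "Multiple logistic regression models will be constructed to explore the variables associated with positive attitudes and practices toward influenza vaccination". Entry is by two routes: "All variables that achieve a p-value of ≤0.2 in the univariate model will be included in the multivariable regression model", and "along with those deemed clinically relevant by the investigators". The significance rule is "All tests will be two-tailed, and a p-value <0.05 will be considered statistically significant". The candidate variables are not listed. No country term, stratum, random effect or clustering is named for the regression. Differences between participating sites are examined only in a separate, unadjusted chi-square or Fisher test.

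The sample is multi-country by design. Study population states: "Physicians from any country who provide care to adult patients were invited to participate in the quantitative survey", and "We aim to reach over 3,500 physicians worldwide". Under Quantitative survey, the link was "distributed via email through the World Heart Federation mailing list and other associated scientific societies". The analysis section adds: "A non-probability snowball sampling will be performed". The Background makes variability across settings an aim, and the Abstract contrasts free vaccine for cardiovascular patients in Argentina with out-of-pocket payment in India.

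**The concern.** A crude odds ratio for specialty, work setting or experience equals the within-country association only if country does not link the factor to the outcome. Two conditions together create that link: attitude or practice differs by country, and the mix of responding physicians also differs by country in a related way.

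The design makes both plausible. Vaccine access differs by country, and the questionnaire itself asks about local prescribers and guideline inclusion. Respondents arrive through whichever societies forwarded the link, and nothing balances specialty or setting across countries.

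Two errors can follow:
- **At the screen.** It is univariate, so country is absent there by construction. A factor that matters within every country can be masked, fail p ≤0.2 and never reach the multivariable model. Adding country later does not bring it back.
- **In the final model.** If country is not among the variables that enter, a factor with no within-country association can appear significant.

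The Discussion expects the results to shape recommendations to practitioners and policy makers, so either error could misdirect them.

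This is separate from correlated responses within countries. Clustered standard errors change the interval but leave the odds ratio where it is.

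**Working it through.** The plan gives no effect size, country rates or country mix, so it has no figure of its own to reproduce.

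**Inputs from the article:** about 3,500 respondents (a recruitment aim), screen at p ≤0.2, two-sided 5% test.

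**Assumed inputs:** two countries of 1,750 each; a binary factor; 80% positive among unexposed physicians in country A and 60% in country B.

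**Formulas.** Crude OR = ad/(bc) from the pooled 2×2 table; SE of log OR = √(1/a + 1/b + 1/c + 1/d). A factor fails the screen when |z| < 1.28.

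**1. A real factor masked at the screen.** True OR 1.5 in both countries; exposure shares 30% (A) and 70% (B).
- Exposed odds in A: 4 × 1.5 = 6, so 85.7% positive. In B: 1.5 × 1.5 = 2.25, so 69.2% positive.
- Exposed, pooled: 0.3 × 0.857 + 0.7 × 0.692 = 0.742.
- Unexposed, pooled: 0.7 × 0.8 + 0.3 × 0.6 = 0.740.
- Crude OR = (0.742/0.258)/(0.740/0.260) = 1.01.
- SE = √(1/1298.1 + 1/451.9 + 1/1295 + 1/455) = 0.077, so expected z = 0.0092/0.077 = 0.12.
- P(fail) = Φ(1.28 − 0.12) − Φ(−1.28 − 0.12) ≈ 0.80, in line with about 80% of 4,000 simulated surveys.

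The same data screened within country: the inverse-variance combined SE is 0.087, so z = ln(1.5)/0.087 ≈ 4.7 and the factor passes almost always.

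Two further cases with the same 80% and 60%:

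| True OR | Shares A/B | Crude OR | Fails screen (simulated) |
|---|---|---|---|
| 1.25 | 40/60 | 1.02 | about 79% |
| 1.5 | 35/65 | 1.11 | about 47% |

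**2. A null factor made significant if country is left out.** True OR 1.0; shares 70% (A) and 30% (B).
- Exposed: 0.7 × 0.8 + 0.3 × 0.6 = 0.74. Unexposed: 0.3 × 0.8 + 0.7 × 0.6 = 0.66.
- Pooled OR = (0.74/0.26)/(0.66/0.34) = 1.47; SE = √(1/1295 + 1/455 + 1/1155 + 1/595) = 0.074; 95% CI 1.27–1.70.
- Shares 60/40 give 1.21 (1.05–1.40). Shares 50/50 give 1.00.

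**3. Many countries.** This simulation used 30 unequal countries, 3,500 respondents, a true OR of 1.0 and 200 runs per scenario. Country effects on outcome and on factor were drawn independently, so they are related only by chance.

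| SD of country log-odds, outcome/factor | False positives, no country | Clustered SE only | Country indicators | Country passes p ≤0.2 |
|---|---|---|---|---|
| none | 4.5% | 5.5% | 5.5% | 16% |
| 0.3/0.5 | 8.0% | 8.0% | 4.5% | 99.5% |
| 0.5/0.5 | 16% | 9.5% | 6.5% | 100% |
| 0.8/0.8 | 39.5% | 9.0% | 7.0% | 100% |

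Simulation error is about 1.5 percentage points near 5%.

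**The case against.** The strongest reply is that the plan does not exclude country. Either entry route can admit it, and the planned comparison across sites suggests that location is available to the analysts. In the simulation, country passed the p ≤0.2 screen in 99.5–100% of runs whenever countries differed. So where the bias would arise, the stated rule would almost always put country in the final model, provided it is a candidate. A factor that entered spuriously would then be re-estimated alongside country. Jurisdiction items on prescribers and guidelines could absorb part of the difference too.

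This reply stands for the final model. A reader might infer that the regression as planned estimates associations across pooled countries and not within them, so that its odds ratios are biased. The text does not say that. High false-positive rates can be produced: 33–92% in a simulation with a country-level correlation of 0.3–0.5 between outcome and factor built in, and 17–66% with clustered standard errors. They describe a final model without country under assumed inputs, not the two-step rule in the article.

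The reply does not reach the screen. A factor dropped because its crude association is masked is not re-estimated unless the investigators happen to retain it.

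It can also be said that a list of candidates is detail an article leaves to the fuller plan. That is fair for the list, but the crude univariate screen is a stated rule. The article acknowledges heterogeneity under Anticipated Limitations as a difficulty for uniform policies, not as confounding of the odds ratios.

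**Conclusion.** The concern holds in this form: the stated screen is not conditioned on country, and country's place in the final model is left to a p-value or to judgement over an unlisted candidate set. The odds ratios may therefore mix within- and between-country differences; the document does not establish that they will.

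Under the assumed two-country inputs, a true odds ratio of 1.5 can shrink to a crude 1.01 and be screened out about four times in five. A null factor can show 1.47 if country is omitted from the final model. Less uneven physician mixes give smaller distortions, and there is no such bias if physician mix is unrelated to country-level outcome. All country rates and mixes are assumptions. The analysis is exploratory, which limits the consequences but does not make the crude screen a good choice for an any-country snowball sample.

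**What to change.** For physician-level factors, force country into every screening and final model regardless of its own p-value, either as country indicators or by conditional logistic regression grouped by country. Group sparse countries by region or income level if needed. Assess jurisdiction-level factors, such as guideline inclusion and who may prescribe or provide the vaccine, in a separate random-intercept model.

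The change is analysis wording and standard commands in the software already named; it needs no new data if respondents' country was recorded. The costs are modest:
- Countries where all or none of the respondents are positive drop out of the within-country estimate (about 0–2% of respondents in a simulation with 40 or 80 assumed countries).
- Grouping sparse countries leaves some residual confounding.
- One extra model has to be fitted and reported.
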